## Abstract

**Background:**

Efficacy and quality of life (QoL) are key criteria for therapy selection in metastatic breast cancer (MBC). In hormone receptor positive (HR +) human epidermal growth factor receptor 2 negative (HER2 −) MBC, addition of targeted oral agents such as everolimus or a cycline-dependent kinase 4/6 (CDK 4/6) inhibitor (e.g., palbociclib, ribociclib, abemaciclib) to endocrine therapy substantially prolongs progression-free survival and in the case of a CDK 4/6i also overall survival. However, the prerequisite is adherence to therapy over the entire course of treatment. However, particularly with new oral drugs, adherence presents a challenge to disease management. In this context, factors influencing adherence include maintaining patients’ satisfaction and early detection/management of side effects. New strategies for continuous support of oncological patients are needed. An eHealth-based platform can help to support therapy management and physician–patient interaction.

**Methods:**

PreCycle is a multicenter, randomized, phase IV trial in HR + HER2 − MBC. All patients (*n* = 960) receive the CDK 4/6 inhibitor palbociclib either in first (62.5%) or later line (37.5%) together with endocrine therapy (AI, fulvestrant) according to national guidelines. PreCycle evaluates and compares the time to deterioration (TTD) of QoL in patients supported by eHealth systems with substantially different functionality: CANKADO active vs. inform. CANKADO active is the fully functional CANKADO-based eHealth treatment support system. CANKADO inform is a CANKADO-based eHealth service with a personal login, documentation of daily drug intake, but no further functions. To evaluate QoL, the FACT-B questionnaire is completed at every visit. As little is known about relationships between behavior (e.g., adherence), genetic background, and drug efficacy, the trial includes both patient-reported outcome and biomarker screening for discovery of forecast models for adherence, symptoms, QoL, progression free survival (PFS), and overall survival (OS).

**Discussion:**

The primary objective of PreCycle is to test the hypothesis of superiority for time to deterioration (TTD) in terms of DQoL = “Deterioration of quality of life” (FACT-G scale) in patients supported by an eHealth therapy management system (CANKADO active) versus in patients merely receiving eHealth-based information (CANKADO inform).

EudraCT Number: 2016–004191-22

## Background

Despite adjuvant therapy improvements in HR + /HER2 − breast cancer, a substantial proportion of patients still progresses to the metastatic stage. In the metastatic setting, when planning a therapy or therapy sequence, the focus is not only on efficacy, but also quality of life (QoL). Recently, some therapies have been approved for MBC to overcome hormone resistance such as everolimus or CDK 4/6 inhibitors (e.g., palbociclib, ribociclib, abemaciclib) which are administered orally.

Palbociclib is the first inhibitor of cyclin-dependent kinases (CDK) 4 and 6 that was approved in breast cancer. In vitro, palbociclib reduced cellular proliferation of ER-positive breast cancer cell lines by blocking progression of cells from G1 into S phase of the cell cycle. Based on the three large studies PALOMA-1, -2, and -3 [1–3], palbociclib was approved for pre- and postmenopausal patients with advanced/metastatic breast cancer who are candidates for aromatase inhibitor or fulvestrant.

The steady increase of oral drugs in anticancer treatment requires changes in patient management. Adherence to therapy over the entire course of treatment is a prerequisite for efficacy. While oral administration provides advantages compared to intravenous application of antineoplastic medications regarding QoL (e.g., flexibility, less wasted time and effort), patient responsibility is higher; there can be a loss of physician assistance and monitoring of the treatment. Maintaining adherence thus presents a challenge to disease management. In this context, factors influencing adherence include QoL factors such as patient satisfaction and early detection/management of side effects. New strategies for continuous support of oncological patients, particularly MBC patients, are needed. An eHealth-based platform such as CANKADO can help to support therapy management by probing the QoL status of the patient continuously throughout the course of treatment and, ideally, providing a basis for intensified care when indicated.

QoL combines different aspects of personal health status of an individual [4]. It represents a multi-domain concept, which includes the patient’s general perception of the effect of illness and treatment on physical, psychological, and social aspects of life. For cancer patients, it is important to determine further aspects such as economic burden, home management problems, or lack of emotional well-being—all of which can adversely affect QoL [5]. An important role of patient-reported outcome (PRO) measurement in cancer care is the determination of negative effects or the identification of needs for supportive care [6].

All these aspects are well covered in the FACT-G scale. The FACT-G as a part of the breast cancer questionnaire FACT-B is multidimensional, consisting of subscales assessing Physical Well-Being (PWB), Emotional Well-Being (EWB), Social Well-Being (SWB), and Functional Well-Being (FWB). The FACT-G yields a total score, as well as individual subscale scores, with higher scores reflecting better QoL [7, 8]. A change from baseline of 5 points or greater is considered a minimally important difference (MID) [9].

Having a continuous PRO feedback can heighten physicians’ awareness of their patients’ QoL [10]. A simplified PRO like a pain scale is feasible for daily documentation and is suited to improve communication between patients and healthcare professionals [11].

Additionally, uncertainty, lack of confidence, or anxieties related to the physician are factors that are known to influence outpatient communication [12]. These factors can even lead to a clinical phenomenon known colloquially as “white-coat hypertension,” particularly in older breast cancer patients (> 50 years) [13, 14]. More seriously, there are indications that patients may be inhibited to report clinical symptoms or discomfort in their entirety during examinations, due perhaps to a psychologically motivated desire to “please” their physician. eHealth platforms can serve to empower patients by overcoming uncertainty and anxiety in physician communication, lowering the threshold for describing symptoms, and ultimately providing more complete patient reports [6, 15].

The “ISPOR ePRO Good Research Practices Task Force” reported that data from an electronic PRO (ePRO) questionnaire adapted from a paper-based questionnaire had equivalent or superior performance (e.g., exhibited higher reliability) than the data from the original paper version [16]. Moreover, ePROs avoid data entry errors and reduce missing data as compared to paper-based PRO, provide immediate access to data, enable triggering alerts/notifications, and increase the patient’s willingness to report potentially sensitive information. In addition, data obtained from ePROs provide real-time tracking of survey compliance [6]. Remarkably, Basch et al. found that ePRO documentation is associated with improved overall survival compared to routine care in cancer patients [17].

Giving patients the opportunity to document complaints and QoL continuously at home provides a more detailed overview about their progress and can be used for directed questions from the physician. It also facilitates a more granular and reliable longitudinal overview. Such reports can improve the understanding of QoL of cancer patients receiving oral therapies.

The PreCycle trial was designed to evaluate the impact of ePROs in MBC using CANKADO (www.cankado.com). CANKADO is designed as an eHealth portal aimed to support therapy management, adherence, and physician–patient interaction [18]. Within PreCycle, CANKADO allows drug intake documentation, supports collection of ePRO data in a highly standardized manner, and provides overview reports to the investigators. These features have the additional advantage of promoting participant retention.

## Material/methods

### Study design

PreCycle (Design: see Figs. 1 and 2) is a multicenter, randomized, parallel-group, phase IV clinical trial. The primary objective is to test the hypothesis of superiority regarding “time to deterioration” (TTD) of QoL for patients using the ePRO system “CANKADO active” compared to those using the “CANKADO inform” version. “CANKADO active” is the fully functional CANKADO-based eHealth treatment support service, including documentation of daily drug intake, daily documentation of QoL, feedback functions (PRO-React), and on-site surveys. “CANKADO inform” stands for a CANKADO-based eHealth service with a personal login. On-site surveys without feedback functions for the patient and documentation of daily drug intake are also available.

**Fig. 1 Fig1:**
[figure not shown]
Schedule of ePRO documentation

**Fig. 2 Fig2:**
[figure not shown]
PreCycle—study design

Information about data entry, coding, and security policies for the CANKADO eHealth system can be found at https://cankado.com/policy.

### Participants

Eligible patients have histologically or cytologically proven diagnosis of HR+ / HER2- locally advanced or metastatic breast cancer and are either candidates to receive palbociclib in combination with aromatase inhibitor or candidates to receive palbociclib in combination with fulvestrant for their locally advanced or metastatic disease. All anticancer treatments used in this study are approved drugs and therapy is in accordance to national treatment guidelines [19]. The trial compares two different kinds of eHealth support and documentation of patient-reported quality of life data.

There is no blinding process used in the study.

For inclusion and exclusion criteria, please refer to Table 1. In patients who are candidates for palbociclib in combination with aromatase inhibitor or fulvestrant, one prior line of chemotherapy for locally advanced or metastatic breast cancer is admissible, in addition to a maximum of two lines of endocrine therapy.

**Table 1 Tab1:** PreCycle**—**inclusion and exclusion criteria

Inclusion criteria	Exclusion criteria
Post- or pre/peri-menopausal female patients, age ≥ 18 years	Known hypersensitivity to aromatase inhibitor, fulvestrant, palbociclib or any of its excipients
Patients with metastatic or locally advanced (non-operable) breast cancer disease	Contraindication for aromatase inhibitor, fulvestrant or palbociclib; or LHTH-agonists (if pre-menopausal)
Patients who are appropriate candidates for aromatase inhibitor + palbociclib combination therapy	Prior treatment with any CDK inhibitor
Patients having already received endocrine therapy who are appropriate candidates for fulvestrant + palbociclib combination therapy	Patients with locally advanced or metastatic, symptomatic, visceral spread, who are at risk of life threatening complications in the short term
One prior line of chemotherapy and/or a maximum of two endocrine therapy lines for locally advanced or metastatic disease is/are allowed	Known active uncontrolled or symptomatic CNS metastases
Peri-/pre-menopausal patients should additionally receive a LHRH-agonist	Current use of food or drugs known to be potent inhibitors or inducers of CYP3A4
The tumor must be hormone-receptor positive	High cardiovascular risk, including, but not limited to recent myocardial infarction, severe/unstable angina, or severe cardiac dysrhythmias in the past 6 months of enrollment
The tumor must be HER2-negative defined as either HER2 immunohistochemistry score 0 or 1 + or as HER2-negative by ISH	Diagnosis of any second malignancy within the last 5 years prior to enrollment, except for adequately treated basal cell or squamous cell skin cancer, or carcinoma in situ of the cervix
Eastern Cooperative Oncology Group (ECOG) performance status 0–2	Participation in other clinical trials involving investigational drug(s) (phases 1–4) within 2 weeks before the current study begins and/or during study participation
Tissue of the primary tumor and metastatic lesion for biomarker study if applicable	Lactating women
Adequate organ and marrow function	Life expectancy < 3 months
In case of patients of child bearing potential: negative serum pregnancy test at baseline. Patients must agree to use highly effective non-hormonal contraception	Known infection with HIV, hepatitis B virus, or hepatitis C virus
Resolution of all acute toxic effects of prior therapy, including radiotherapy grade < 1 (except toxicities not considered a safety risk for the patient) and recovery from surgical procedures	Concurrent severe, uncontrolled systemic disease, social or psychiatric condition that might interfere with the planned treatment and with the patient’s adherence to the protocol
Willingness and capability to use CANKADO	Legal incapacity or limited legal capacity
Availability of hardware: computer and/or tablet and/or smartphone with internet access	
Signed written informed consent	

Patients are stratified according to their eligibility for receiving palbociclib with endocrine therapy (AI or fulvestrant) as first or later lines.

The study includes a variety of different centers and clinical settings in Germany (university, community hospitals, private practice). More information including participating sites can be found at http://www.precycle.info.

### Treatment, stratification, randomization, data

Patients allocated to the combination of palbociclib with aromatase inhibitor receive:Palbociclib, 125 mg, orally once daily on day 1 to day 21 of every 28-day cycle followed by 7 days off treatment andAromatase inhibitor, orally once-daily (continuously).Pre- or peri-menopausal patients should additionally receive a LHRH-agonist

Patients allocated to the combination of palbociclib with fulvestrant receive:Palbociclib, 125 mg, orally once daily on day 1 to day 21 of every 28-day cycle followed by 7 days off treatment andFulvestrant, 500 mg, intramuscularly on days 1 and 14 of cycle 1, every 28 days (± 7 days) thereafter starting.Pre- or peri-menopausal patients should additionally receive a LHRH-agonist

Participants are randomly assigned to either experimental (“CANKDO active”) or control group (“CANKADO inform”) with a 2:1 allocation as per a computer-generated randomization schedule stratified by site and prior therapy line (first line vs. later line) using permuted blocks of random sizes. The block sizes are not disclosed, to ensure concealment. Randomization lists are created by the sponsor biostatistics department and forwarded to the sponsor randomization center. Figure 2 illustrates the expected patient distribution across strata and arms.

Patient assignment to the PreCycle study arms is managed centrally by a combined process involving the CANKADO system and the eCRF. After a patient has signed the ICF and screening measurements have been completed, patient baseline data have to be documented in eCRF by site personnel. Then, the site creates a patient account in CANKADO. The CANKADO system generates a patient-specific CANKADO trial ID which is part of the baseline documentation at the eCRF. The patient-specific CANKADO trial ID is the link between the two systems. When baseline documentation is completed, the site can request patient enrollment at the sponsor randomization center via phone or email. The randomization center assigns the study arm according to site specific randomization lists via eCRF and in parallel to the patient account in the CANKADO system. Afterwards, the site activates patient’s CANKADO account.

Patients continue to receive study treatment together with the assigned ePRO assessment until investigator assessed disease progression, symptomatic deterioration, unacceptable toxicity, death, or withdrawal of consent, whichever occurs first.

Adverse events (AEs) and serious adverse events (SAEs) are collected throughout palbociclib treatment and 28 days after the last dose. When an AE/SAE occurs, it is the responsibility of the investigator to review all documentation (e.g., hospital progress notes, laboratory reports, and diagnostics reports) related to the event. The investigator then record all relevant AE/SAE information in the eCRF.

Patients discontinuing the active treatment phase enter a follow-up period phase; further progression and new anti-cancer therapy information are collected once a year up to 48 months after randomization.

In addition, biomarkers are assessed as a scientific translational program within this study. Tumor material from available primary tumor and/or available biopsies from recurrent disease are collected. Blood samples are collected at four time points during the study when also routine blood samples are mandatory (see Fig. 3).

**Fig. 3 Fig3:**
[figure not shown]
PreCycle—schedule of investigations

All study treatments are approved treatments following clinical standards and local guidelines.

### Statistical considerations

The primary endpoint is time to deterioration (TTD) of quality of life (QoL), based on the FACT-G instrument total score. This time is defined as the interval from registration until a DQoL (deterioration of quality of life) event, determined using the FACT-G scale (or censoring). Measurements are taken at day 1 of each 28-day treatment cycle in both arms. The event “deterioration of quality of life (DQoL)” is defined as any decrease of 10 or more points from baseline unless a recovery is achieved in the subsequent assessment. A recovery is defined as a QoL score no worse than 9 points below baseline. If data of the subsequent visit is missing, a decrease of 10 or more points will be considered as an event. The study tests the hypothesis of superiority of TTD in patients supported by eHealth therapy management in arm A compared to arm B.

Sample size was estimated as follows: the superiority hypothesis test for DQoL is based on the stratified score function test of a Cox regression model with Breslow likelihood, including therapy line stratum as covariate. Assuming a (constant) hazard ratio of 0.8 for TTD in arm A vs. arm B, the study is designed to refute the null hypothesis of equal survivor functions between arm A and arm B at a two-sided 5% significance level [20, 21] with at least 80% power.

Patients in the strata defined above are referred to here as “first-line” and “later-line” patients. First-line patients are assumed to comprise about 5/8 (62.5%) of the entire trial population; the remaining patients (3/8, i.e., 37.5%) are assumed to be treated in later lines. In first-line patients, the proposed hazard ratio between CANKADO arms of 0.8 corresponds to about 4 months superior TTD for CANKADO active; in later-line patients, it corresponds to about 2 months superior TTD. Such an increase is assumed to have a clinically relevant benefit.

To estimate a *lower* bound for the expected number of DQoL (deterioration) events, we assume that, at the very least, disease progression will generate a DQoL event. Therefore, the median PFS reported in the PALOMA-1 and -2 trials (first-line patients treated with palbociclib and letrozole) [1, 2], as well as PALOMA-3 (2nd line patients treated with palbociclib and fulvestrant) [3] may serve as model for first-line and later-line strata here. Consequently, we used the upper confidence limit for median PFS reported in PALOMA-1 (27.5 months) [1] and PALOMA-3 (11 months) [3] to compute conservative estimates for the expected number of events in the first-line and later-line stratum respectively.

During the conduct of the study no interim analysis is planned.

The primary analysis implements the intent-to-treat principle (ITT). Primary reporting is based on the ITT population of all randomized patients, including patients with protocol violations and intercurrent events, handled by a while-on-treatment strategy. An additional sensitivity analysis will be carried out based on a per-protocol population excluding patients with major protocol violations (to be determined during data review prior to database lock based on prospectively defined criteria). For the primary analysis, missing values are treated as missing-at-random by therapy line and treatment arm strata. Patient information entering the analysis will be either time of censoring (e.g., administrative censoring or intercurrent event) or the actual event time.

The sample size was estimated using a validated Monte-Carlo simulation implemented in Python 3.5. In all 4 groups (2 arms with 2 strata each), exponential survival was used as parametric sampling distribution with hazard rate computed from median PFS estimates as indicated above. In addition, an independent exponential censoring process was used to simulate loss to follow-up with 48-month probability of censoring calibrated at 10%.

If 960 patients are recruited (assuming 10% loss to follow-up), we can expect to reject the null-hypothesis with 80% power if a stratified two-sided test of equal hazards between (CANKADO active) and (CANKADO inform) is performed at alpha = 0.05. The corresponding expected number of events across groups is 693.

For each stratum and arm, Kaplan–Meier product-limit estimators of the survivor functions together with Hall-Wellner confidence bands will be reported and visualized graphically. In addition, corresponding median TTD with log-transformed 95% confidence will be reported.

Secondary endpoints include a definition of TTD of QoL as minimally important difference (5-point drop from baseline on FACT-G scale) to provide a sensitivity analysis with respect to the primary endpoint, progression-free survival and overall survival as clinical outcomes, as well as ePRO measurements of global health status and FACT-B scales. Translational research questions will focus on the influence of genetic and immune biomarker profiles on clinical outcome.

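### The primary Cox test adjusts for therapy line only; prespecifying baseline FACT-G as a covariate would be a low-cost efficiency gain of uncertain size

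*Protocol article*

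**What the plan says.** All of this is in the protocol article, section Statistical considerations, unless stated otherwise.

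- **Primary test:** a "stratified score function test of a Cox regression model with Breslow likelihood, including therapy line stratum as covariate". Whether therapy line acts as a stratum or as a covariate, it is the only adjustment factor named.
- **Event:** "any decrease of 10 or more points from baseline unless a recovery is achieved in the subsequent assessment". Both the visit with the drop and the visit that checks recovery are compared with the same baseline score.
- **Design effect and level:** "Assuming a (constant) hazard ratio of 0.8 for TTD in arm A vs. arm B", tested "at a two-sided 5% significance level".
- **Power:** with 960 patients, "we can expect to reject the null-hypothesis with 80% power". "The corresponding expected number of events across groups is 693".
- **Randomisation** (section Treatment, stratification, randomization, data): 2:1, stratified by site and therapy line, not by baseline FACT-G.

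The article gives no FACT-G standard deviation, no reliability and no association between baseline score and time to deterioration. It does not claim any adjustment for baseline.

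**The concern.** The endpoint is a fall of fixed size from one measured score. If that score is high by chance, the threshold sits too high at every later visit and the event is easier to reach. If it is low by chance, the event is harder to reach. Requiring that the next visit shows no recovery does not remove this, because the reference score is the same. Scale limits act in the same direction, since a patient who starts low has less room to fall. A clinical effect may run the other way, since patients who start low may be sicker and deteriorate sooner. The net effect is plausibly not zero, but its strength and shape are unknown.

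In a Cox model, leaving out a prognostic covariate pulls the treatment hazard ratio towards 1. At stake is some power that could be had from data already needed to compute the endpoint, in a design with little margin above 80%.

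**Working it through.** **Inputs from the article.** 960 patients, 2:1; 5/8 first line (600) and 3/8 later line (360); medians 27.5 and 11 months; HR 0.8; two-sided 5%; exponential loss calibrated to 10% at 48 months; 48 months of follow-up.

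**Step 1: reproduce the 693 events.** Take the medians as those of the control arm. The loss rate is λ = −ln(0.9)/48 = 0.002195 per month. For hazard h, P(event) = h/(h+λ) × [1 − exp(−48(h+λ))].

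| Group | n | h | P(event) | Events |
|---|---|---|---|---|
| First line, inform | 200 | 0.02521 | 0.673 | 134.6 |
| First line, active | 400 | 0.02016 | 0.594 | 237.4 |
| Later line, inform | 120 | 0.06301 | 0.924 | 110.9 |
| Later line, active | 240 | 0.05041 | 0.882 | 211.6 |

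The total is 694.5, against 693 stated. Putting the medians in the active arm gives 755, which does not match.

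**Step 2: reproduce the 80% power.** By Schoenfeld, power = Φ(|ln HR| × √(D × 2/3 × 1/3) − 1.96). With D = 693: 0.2231 × √154 = 2.769; 2.769 − 1.96 = 0.809; Φ = 0.791. Simulating the line-stratified Cox test gives 0.80 to 0.82. The plan's figures hold for the plan's test.

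**Step 3: add a baseline effect (assumption).** Let g be the log hazard per SD of baseline FACT-G, with a normal covariate and a log-linear effect. There were 3,000 simulated trials per row, with both models fitted to the same trials; Monte Carlo error is about 0.7 points per power. Here the HR conditional on baseline is held at 0.80.

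| g | Hazard factor per SD, exp(g) | Unadjusted HR | Power without baseline | Power with baseline | Gain (points) |
|---|---|---|---|---|---|
| 0 | 1.00 | 0.798 | 0.815 | 0.817 | 0.2 |
| 0.1 | 1.11 | 0.801 | 0.788 | 0.795 | 0.7 |
| 0.2 | 1.22 | 0.801 | 0.793 | 0.810 | 1.7 |
| 0.3 | 1.35 | 0.806 | 0.775 | 0.812 | 3.7 |
| 0.4 | 1.49 | 0.814 | 0.728 | 0.789 | 6.1 |
| 0.5 | 1.65 | 0.821 | 0.685 | 0.787 | 10.2 |

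Further runs agree within simulation error: 81% against 82% at 1.2 per SD (1,000 runs); 75% against 80% at 1.35, 74% against 80% at 1.5, and 78.6% for both models with no baseline effect (2,000 runs).

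**Step 4: the same with the unadjusted HR held near 0.80.** Power without and with baseline is 0.802 and 0.799 at g = 0; 0.812 and 0.812 at 0.1; 0.782 and 0.807 at 0.2; 0.782 and 0.819 at 0.3; 0.795 and 0.858 at 0.4; 0.793 and 0.882 at 0.5.

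**Step 5: what g is plausible?** A rough score model of confirmed 10-point drops, with assumed between-patient SD of 12 to 14 points, per-visit error SD of 3 to 7 points and slow drift, gave g of about 0.08 to 0.49 (factor 1.08 to 1.63). A variant with SDs of 12 to 15 and 4 to 7 gave 0.16 to 0.32 (1.17 to 1.38). Neither includes sicker low scorers, which would reduce g. They support the direction and leave the size open.

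**The case against.** **A line-stratified test is conventional, and nothing here is wrong.** This stands. The test matches the stratified randomisation, is the test that was powered, and reproduces. Covariate-adjusted supportive analyses may also be in the analysis plan, which is not shown.

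**A reader might infer that the trial is underpowered.** The article does not support that. Its 0.8 is the ratio between arms, simulated within line and not conditional on FACT-G. Held to that (step 4), the planned test keeps roughly 78% to 81% power at every g shown, and adjustment lifts power above the target. The unadjusted figures below 80% in step 3 come from holding the conditional ratio at 0.80 instead. Nor does this point cast doubt on the event count, since 693 reproduces.

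**A reader might call baseline FACT-G strongly prognostic.** The article gives nothing to establish that. At 1.75 per SD the contrast is larger, 67% against 79%, but that factor lies outside the range in step 5.

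**A reader might fear that chance imbalance distorts the result.** The SE of the baseline difference is √(1/640 + 1/320) = 0.068 SD. At g = 0.3, a one-SE imbalance shifts the log HR by 0.3 × 0.068 = 0.02, against an SE of the log HR of 1/√154 = 0.08. The test's type I error already allows for this.

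**Adjustment is not entirely free.** This stands. In a Cox model it does not shrink the SE of the log HR. The gain comes from targeting a conditional ratio further from 1, so the estimand changes slightly and a functional form must be fixed in advance.

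**Conclusion.** The point holds as an efficiency improvement. The primary test leaves out a covariate that is already collected, enters every event threshold and is plausibly prognostic. With a conditional HR of 0.80, the gain is about 0 to 1 point of power if one SD of baseline changes the hazard by 1.2 or less, about 4 points at 1.35 and about 6 points at 1.5, with no loss if baseline is not prognostic. Confidence is good that the covariate is omitted and that adjustment does no harm to power. It is moderate on direction, since sicker low scorers could offset the effect, and low on size, since g is assumed and the simulation used a log-linear effect. The planned analysis remains valid and has its stated power without the change.

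**What to change.** Before database lock, and without reference to outcome data by arm because the trial is open-label, specify the primary analysis as a Cox model stratified by therapy line with baseline FACT-G total as a continuous covariate in a fixed functional form, for example a spline with prespecified knots. Keep the unadjusted line-stratified test as supportive, together with the Kaplan-Meier curves and median times already planned by stratum and arm.

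The cost is a short amendment and no new data. The primary hazard ratio becomes conditional on baseline, so the report should give the unadjusted ratio beside it. The amendment should say how a randomised patient without a baseline score enters the model; such a patient cannot have the event as defined under either analysis. The sample size need not change.

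### The 693 events and 80% power are not secured for the endpoint as defined, because the sample size counts every progression as a DQoL event and the endpoint counts only a FACT-G drop

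*Protocol article*

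**What the plan says.** All references are to the protocol article.

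- **Event rate for planning** (Statistical considerations). The lower bound on events rests on this premise: "we assume that, at the very least, disease progression will generate a DQoL event". Exponential hazards are then taken from the upper confidence limits of median PFS in the cited trials, 27.5 months for first line and 11 months for later line. The only censoring process described for the simulation is loss to follow-up, set at 10% by 48 months.
- **Result** (same section). With 960 patients, "we can expect to reject the null-hypothesis with 80% power", and "The corresponding expected number of events across groups is 693". The effect is set out as "Assuming a (constant) hazard ratio of 0.8 for TTD in arm A vs. arm B", tested at a "two-sided 5% significance level".
- **Endpoint** (same section). The DQoL event "is defined as any decrease of 10 or more points from baseline", unless the next assessment shows recovery. If the next visit is missing, a measured fall of that size still counts. FACT-G is scheduled on day 1 of each treatment cycle.
- **End of assessment** (Treatment, stratification, randomization, data). "Patients continue to receive study treatment together with the assigned ePRO assessment until investigator assessed disease progression", or another listed reason for stopping. For the follow-up phase, only yearly progression and new-therapy information is listed.
- **Analysis** (Statistical considerations). Intercurrent events follow a while-on-treatment strategy. "Patient information entering the analysis will be either time of censoring (e.g., administrative censoring or intercurrent event) or the actual event time".

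**The concern.** The event that was simulated is not the event that is defined. In the simulation a progression is always an event. Under the endpoint definition it is an event only if a FACT-G form records a fall of 10 or more points. The ePRO assessment runs until progression, no FACT-G is listed for follow-up, and intercurrent events are given as an example of censoring. A progression without a recorded fall would therefore seem to leave a censored record. The missing-visit rule does not help such a patient, because it needs a fall that has already been measured.

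If so, progression removes patients from risk as well as being the supposed source of guaranteed events. A lower bound has to hold without help from other sources of events, and this one does not. At stake is whether the event count and power stated for the primary test describe the test that will be run.

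**Working it through.** **Inputs.** From the article: N = 960, allocation 2:1, strata 5/8 and 3/8, medians 27.5 and 11 months, HR 0.8, 10% loss by 48 months, 48 months of follow-up, two-sided alpha 0.05. Group sizes are 400 active and 200 inform in first line, and 240 and 120 in later line. The medians are placed on the control arm, which is the placement that reproduces the stated count. On the active arm they give 755 events, and with the same medians in both arms 737.

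**Step 1: reproduce the plan's figure.**

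Control hazards: ln 2/27.5 = 0.02521 and ln 2/11 = 0.06301 per month. Active hazards: 0.8 times these, 0.02016 and 0.05041. Loss hazard: μ = −ln(0.9)/48 = 0.002195.

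Expected events per group = n · λ/(λ+μ) · [1 − exp(−48(λ+μ))]

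| Group | n | Events |
|---|---|---|
| First line, active | 400 | 237.4 |
| First line, inform | 200 | 134.6 |
| Later line, active | 240 | 211.6 |
| Later line, inform | 120 | 110.9 |
| Total | 960 | 694.5 |

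The article states 693. Power by Schoenfeld, with allocation factor (2/3)(1/3) = 2/9:

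Φ(|ln 0.8| · √(693 × 2/9) − 1.96) = Φ(0.2231 × 12.41 − 1.96) = Φ(0.81) = 79%

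A Monte Carlo run of the stratified score test (10,000 replicates) gives 79.9%. The arithmetic is sound. The match requires that every modelled progression is an event and that progression censors nobody.

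**Step 2: reserve.** Events needed for 80% at 2:1 are (1.96 + 0.8416)²/[(2/9)(ln 0.8)²] = 7.849/(0.2222 × 0.04979), about 710. At 693 there is nothing to spare.

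**Step 3: illustrative ranges.** The article gives no rate of FACT-G deterioration, so f and r below are assumptions. HR 0.8 is kept throughout.

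*(a) A share f of the modelled progressions carries a qualifying fall and the rest are censored.* Events = f × 694.5.

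| f | Events | Power (Schoenfeld) | Power (simulated) |
|---|---|---|---|
| 0.9 | 625 | 75% | 76% |
| 0.8 | 556 | 70% | 71% |
| 0.7 | 486 | 64% | 65% |
| 0.5 | 347 | 50% | 52% |

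*(b) Deterioration has its own control hazard, r times the PFS hazard, and progression (medians 27.5 and 11 months) is independent censoring.* The Step 1 formula applies, with λ multiplied by r and the progression hazard added to μ.

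| r | Control DQoL median, first / later line (months) | Events | Power (Schoenfeld to simulated) |
|---|---|---|---|
| 1 | 27.5 / 11 | 404 | 56-58% |
| 2 | 13.8 / 5.5 | 580 | 72-74% |
| 3 | 9.2 / 3.7 | 674 | 78-79% |

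Under (b), 693 events are reached at about r = 3.3, a control DQoL median of about 27.5/3.3 = 8.3 months in first line and 11/3.3 = 3.3 months in later line.

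**The case against.** The strongest reply has four parts.

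1. **Censoring at progression is not stated.** This stands. The article does not name progression as an intercurrent event. The reading comes from combining the treatment, follow-up, endpoint and censoring text.
2. **A FACT-G form may be completed at the progression visit.** This also stands as a possibility. The abstract has the questionnaire completed at every visit, and the ePRO and investigation schedules (Figs. 1 and 3) are not shown. Such a form would let progression produce an event, but only in patients whose score had fallen by 10 or more points. It would not make every progression an event.
3. **The premise is declared as an assumption, the medians are upper confidence limits, and falls before progression from toxicity or symptoms add events.** All true, so the net error could go either way. But the upper limits protect against slow progression, not against progression without a fall. Earlier falls may fill the gap, but they do not make the figure a lower bound.
4. **The values of f and r have no source in the document, and model (b) makes deterioration independent of progression, contrary to the plan's premise.** Correct. Range (a) stays closer to that premise and gives a milder loss. Both are illustrations, not estimates.

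A reader might infer that the trial is underpowered, or that 693 events will not be reached. The article does not support either: with deterioration frequent enough (r about 3.3 in model (b)), 693 is attainable.

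**Conclusion.** The concern holds as a mismatch between the sample-size assumption and the endpoint. It is not an arithmetic error, since the stated figures follow from their inputs. Neither the lower-bound claim nor the 80% power follows for a FACT-G-only endpoint; they are unsecured rather than shown to be false.

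With no reserve, losing 10% of the modelled events takes power to about 75%, and losing 30% to about 64%. With deterioration as a separate process, power runs from 56-58% at r = 1 to 78-79% at r = 3. These sizes rest on exponential times, HR 0.8 for the events that count, and the inferred censoring at progression. The test, alpha level and endpoint definition are unaffected.

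This is not a matter to leave to the SAP: the article itself states the assumption, the endpoint, the censoring rule, the event count and the power, and they do not fit together.

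**What to change.** - Delete the lower-bound claim.
- Re-run the existing simulation for the endpoint as defined: FACT-G fall only, with progression, death and treatment stop as censoring. Restate expected events, power and detectable HR over a range of deterioration rates.
- Anchor that range on the pooled, arm-blind DQoL rate in the almost 500 patients that the Discussion reports as recruited.
- State in the text how progression and death are handled in the primary analysis. If either is meant to be an event, put it in the endpoint definition and restate the HR and power for that composite. HR 0.8 would then have to be justified for progression or death as well as for FACT-G.

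**Cost:** one re-run and a text amendment. No alpha is spent, because only pooled rates are used, and the restatement itself adds no patients. The drawback is that the stated power may become less favourable.
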